### Calculation of sample size or available sample sufficiency

Considering the financial and human resources for the project as well as the low prevalence of events of interest, we chose to establish the sample size by convenience (pragmatic sample size). In this context, time to select women who will participate was the decisive factor for sample size. Sample size in one study in the same field was 44. Given the amount of available resources, we fixed the post-intervention time in six months. Thus, given the selection period of time, 40 women is the number estimated (20 before intervention and 20 after intervention).

### Ethical and equity aspects

This study is in accordance with the Helsinki Declaration [37] and follows the guidelines and norms of the National Health Council [38] order number 4666/12. The data collected (interviews, scales that were translated to Brazilian Portuguese, scales that were validated by Brazilian investigations) will be exclusively used for academic research. The identity and privacy of the participants will be respected.

Each participant (women who lost their child, professional and managers) will receive two copies of the informed consent form. They will provide information about the study and the research staff’s phone number and emails. This document will be read and signed in case of agreement. The participant and the researcher will keep one copy.

Women who present any risk to their mental health will be forwarded to psychological/psychiatric assistance according to their city of origin. In case they are diagnosed by the health care establishment staff, the respective protocols will be followed. Should diagnosis be known during the second interview, the researcher will send the participant’s personal information (name, birthday, national health identification, mother’s name, and hometown) to the XIII Regional Health Department, under the care of the respective health care professional. This professional will take the appropriate measures so the case may be followed up accordingly.

Notably, this study will not offer participants any significant risks. The results will be applied to benefit perinatal loss assistance all over the country. Additionally, this investigation aims to promote equity, which might be reached when local protocols are used. They will take into consideration the most important aspects of the supportive guidelines, as the assistance provided is personalized, respectful and dignifying. Thus, the patient’s physical and emotional necessities are addressed.

#### Project management

The project management will be carried out by University of São Paulo researchers, as well as the Steering Committee and the Security and Data Monitoring Committees. The Technical Advisory committee will be held by a researcher from São Carlos Federal University and a specialist of “4 Estações Psychology Institute”^4^ a grief institute in the city of São Paulo. The data analysis committee will be held by all researchers.

### Data management and analysis

#### Data analysis plan

The data will be analyzed by the project staff and, whenever necessary, by experts. The analysis plan as well as a detailed plan for statistical analyses will be designed before data collection starts. Qualitative thematic analysis will be applied on the data from the questionnaire, considering the pre-determined categories and new categories the analysis will provide. The data regarding the focus groups will be treated likewise.

#### Descriptive analysis

Descriptive analysis will be based on the qualitative thematic analysis and harm frequency identified by *The Perinatal Bereavement Safety Thermometer* developed for this investigation (Fig. 3).

**Fig. 3 Fig3:**
[figure not shown]
Perinatal Bereavement Safety Thermometer: Harm Checking

*The perinatal bereavement safety thermometer* provides a harm checking of 10 important aspects that impacts the maternal mental health and the grieving process. It is based on the British *Safety Thermometer*s tools developed by the National Health Service (NHS) created for harm checking in five different areas [39].

According to the tool proposed for this study, low temperatures of harm offer a better chance for a healthy perinatal bereavement, once it promotes better memories for the mourning process and the bereavement experience. In the same way, we assumed that an ideal health care assistance should avoid situations that may be interpreted as harm. All the ten items predicted on this tool are considered central and take part on British [14] and/or Canadian [15] guidelines.

Descriptive analysis will be performed to reveal harm frequencies (Fig. 3) caused by health care assistance that did not observe the supporting guidelines for perinatal loss. This analysis will also show the relation between these harms and the findings provided by the three tools used to verify women’s mental health and grieving process.

Thematic analysis will also be carried out by exploring the findings related to the objectives of this investigation. They will be compared with each group and among the groups. The analysis will consider cultural and gender issues. It will also contemplate institutional specificities that will guide the implementation of the protocol in each maternity ward involved in the project.

The qualitative thematic analysis was chosen due to the fact that it is possible to map, analyze and identify pattern (topics) in the data. It has the following steps: 1) data organization; 2) pattern, topic and category mapping; 3) emerging hypotheses testing and 4) alternative explanations gathered from (pre-intervention, post-intervention and focus) groups, as well as from comparative analysis of the groups.

#### Quantitative analysis

A detailed plan for statistical analysis will be developed by the researchers before data collection starts. A modelling plan will be developed and implemented by a team of experts that includes biostatisticians, psychologists and obstetricians.

Simple frequencies will be calculated, and a comparison method will be used (T Student or Chi Square tests).

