#### B) Research instruments and data sources

Data will be collected from women interviewed and from the focus group offered to professionals. We will use a questionnaire specially designed for this project, as well as validated tools used in previous mental health and bereavement studies. Pilot interviews were performed as a way to validate the questionnaire and organize the interview process.

Three scales, that were adapted and validated to Brazilian Portuguese, will be applied:*Perinatal Grief Scale (PGS)*The PGS presents 33 self-applicable psychometric assertions, divided into three subscales, related to perinatal grief adaptation symptomatology. Involves a five-point Likert Scale ranging from “strongly disagree” to “strongly agree”. The cut-off score that we will use is 90, as validated by Paris et al. [34, 35] for the Brazilian population.*Edinburgh Postpartum Depression Scale (EPDS)*The EPDS is a set of 10 self-applicable screening questions, each of them with four multiple choice responses, which indicates the intensity of depressive signs and symptoms that are present during the last seven days before the application. The cut-off score that suggests the woman is probably depressed (or with depression symptoms) is ≥ 11, as validated by Santos for the Brazilian population [35].*Depression Anxiety Stress Scale-21* (DASS-21)DASS-21 is a self-applicable scale with seven items each. It assesses depression, stress and anxiety, considering the previous week. The answers are given in a four-point Likert Scale that vary from 0 (totally disagree) to 3 (totally agree). Score variations correspond to symptom levels such as “normal” and “severe”. The global scores for the three constructs (depression, stress and anxiety) will be calculated as validated by Vignola et al. for the Brazilian population [36].

A sociodemographic questionnaire designed to collect personal data, behavioral information, medical history and information about care received will also be applied.

Each maternity ward will assign the *Reference Professionals* and the *Bereavement Professionals* among their employees.

Data will be provided by each health care establishment. They will send a list containing the stillbirth and neonatal death list, provided by the respective Reference Professionals. The researcher will contact each candidate to verify eligibility for this study, inviting them to participate and scheduling a meeting.

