## Primary and secondary outcomes

### Primary outcomes

A composite of a grief state (grief adaptation symptoms) and rates of depression, stress and anxiety.

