### Variables

#### Variables of interest (***Table ******2***)

**Table 2 Tab2:** Variables of interest

	Variables of interest	Data source	Statistical methods
Sociodemographic data:	Age; Marital Status; Schooling; Socioeconomic status; Skin color; Job; Religion	Questionnaire	Descriptive analysis Frequency analysis
Characteristics/ Personal and behavioral information	Recreational activities (sports and artistic activities); Practices sports; Uses drugs (alcohol, cigarettes and/or illegal drugs; Is under medication and/or psychiatric treatment; Participates in religious groups; Undergoes psychotherapy; Participates in bereavement support groups	Questionnaire	Descriptive analysis Frequency analysis
Health history	Gestational age; Miscarriage, abortion, stillbirth or neonatal previous deaths; Illnesses before gestation; Illnesses in the present gestation; Fetal malformation; Childbirth complications	Questionnaire	Descriptive analysis Frequency analysis
Intervention assessment data	Satisfaction with the assistance given	Questionnaire	Descriptive analysis Frequency analysis
	Perception level regarding anxiety, stress, depression and port-partum depression	Edinburgh Postpartum Depression Scale Depression Anxiety Stress Scale-21	Descriptive analysis Frequency analysis
	Perception level regarding signals (symptoms and feelings) of bereavement	Perinatal Grief Scale	Descriptive analysis Frequency analysis
	Difficulties with life routine resumption	Perinatal Grief Scale	Descriptive analysis Frequency analysis

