5	Professionals and employees may feel some discomfort or find the guidelines morbid	The Reference Professional will help the professionals and the staff adjust to the new routine. More adapted professionals may join the staff to help transition
6	Difficulties regarding continuous care after hospital discharge	The professional from Regional Health Department XIII (Woman Health) will follow up on the implementation of the project and will address this problem
7	The maternity ward does not want to share data (women’s telephone numbers, emails, etc.)	The Project management staff understand that in the event the maternity ward does not want to share data, it may be included in the staff training, but not in data collection. Training and data collection are not imbricated

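### The primary outcome is worded as rates and the test is left as t or chi-square; name the scale scores, adjusted for ward and type of loss, as the main comparison

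*Protocol article*

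**What the plan says.** Under Primary outcomes, the protocol article gives: "A composite of a grief state (grief adaptation symptoms) and rates of depression, stress and anxiety". The section on research instruments fixes thresholds for two of the three scales. For the PGS, "The cut-off score that we will use is 90"; for the EPDS, "The cut-off score that suggests the woman is probably depressed (or with depression symptoms) is ≥ 11". For the DASS-21 the same section says that global scores for the three constructs will be calculated, and it also mentions symptom levels.

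The Quantitative analysis section names the comparison in one sentence: "Simple frequencies will be calculated, and a comparison method will be used (T Student or Chi Square tests". It does not allocate the tests to outcomes and names no covariate. It also promises a detailed statistical plan and a modelling plan, whose content is not shown. In Table 2 the methods column for the three scales reads "Descriptive analysis Frequency analysis", with no comparison listed.

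The sample is "40 women is the number estimated (20 before intervention and 20 after intervention", and of its size the article says "we chose to establish the sample size by convenience (pragmatic sample size". The groups are the first 20 women in each period who accept, drawn from four wards, after either stillbirth or neonatal death. Table 4 provides that a ward unwilling to share data is handled as follows: "it may be included in the staff training, but not in data collection".

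**The concern.** The three scales are multi-item scores. Classifying each woman only as above or below a threshold discards how far above or below she is. With 40 women, fixed by resources rather than by a power calculation, that loss cannot be made up by recruiting more. The outcome wording and the cut-offs point towards comparing rates, while the analysis sentence allows either rates or scores. The choice that most affects what the study can detect is therefore open in the text that readers will hold the study to.

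Both named tests are also unadjusted, although period rather than randomisation forms the groups. Nothing balances ward or type of loss between periods, and Table 3 does not list a change of case mix among its biases. If the share of neonatal deaths, or of women from one ward, differs between periods, an unadjusted comparison would count that difference as an effect of the guidelines.

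**Working it through.** **The plan's own figure.** There is none to reproduce. The 40 rests on resources and a six-month post-intervention period, with no alpha, power or effect size stated.

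**Inputs from the article.** n = 20 per group, independent groups; four wards (3 df as a covariate); two types of loss (1 df).

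**Assumptions.** Two-sided alpha 0.05; normally distributed scores with equal SD; a shift of d SD between periods; a share p1 above the cut-off before the intervention of 50–80%, with 30% as a check.

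**Score by t test.** The noncentrality is d × √(n/2) = d × √10, with 38 df and critical value 2.024.
- d = 0.9: noncentrality 0.9 × 3.162 = 2.846, power 79%.
- d = 0.6: noncentrality 1.897, power 46%.

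**Cut-off by chi-square or Fisher.** The same shift gives p2 = Φ(Φ⁻¹(p1) − d). Power comes from exact enumeration of all 21 × 21 tables, with the chi-square uncorrected.

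| d | p1 → p2 | t on score | Chi-square | Fisher |
|---|---|---|---|---|
| 0.9 | 50% → 18% | 79% | 58% | 46% |
| 0.9 | 70% → 35% | 79% | 58% | 46% |
| 0.9 | 80% → 48% | 79% | 59% | 47% |
| 0.6 | 50% → 27% | 46% | 31% | 21% |
| 0.6 | 70% → 47% | 46% | 30% | 21% |
| 0.6 | 80% → 60% | 46% | 30% | 20% |

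With p1 = 30% the cut-off does worse: at d = 0.9, chi-square has 45% power and Fisher 32%.

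**Information kept by a cut-off.** The efficiency relative to the score is φ(x)²/[q(1 − q)], where q is the share above the cut-off and x = Φ⁻¹(q). It is 64% at q = 50%, 58% at 70% and 49% at 80%. So 36% to 51% of the information is lost.

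**Detectable difference at 80% power.** The score needs 0.91 SD. Chi-square needs a fall such as 50% to 11%, 70% to 26% or 80% to 37%. The 95% CI half-width for an unadjusted mean difference is 2.024 × √(2/20) = 0.64 SD.

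**Cost of adjusting.** Ward and type of loss together spend 3 + 1 = 4 df, leaving 34.
- Covariates explain nothing (R² = 0): the detectable difference moves from 0.909 to 0.912 SD. Power at d = 0.9 goes from 79.2% to 79.0%.
- R² = 0.2 (assumed): the detectable difference is 0.82 SD.
- Covariates imbalanced between periods (variance inflation of 1.1 assumed, R² = 0): power at d = 0.9 is about 75%.

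**The case against.** A reader might infer that the plan commits to chi-square on dichotomised scales, or gives itself two tries per scale. The text does not support either. Student's t is named first, no scale is assigned to chi-square, and DASS-21 scores are to be calculated. An ordinary reading is t for scores and chi-square for the categorical variables, of which there are many: work absence, psychiatric treatment, admission, and questionnaire items.

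Nor can it be said that the study will be unadjusted, because the promised modelling plan may add covariates. Table 2 does not plainly contradict the analysis section either. It lists descriptive methods for every row and excludes nothing, so it is incomplete.

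Rates also serve a stated aim, since the secondary objective concerns prevalence before and after. Making the score the main comparison therefore changes the wording of the primary outcome, not just the analysis. The article also expects its work to result in a pilot study, and even the score analysis reaches 80% power only for a large difference.

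These points stand, and they limit the finding to a choice left open. They do not settle that choice. Whatever the unseen plan contains, the published primary outcome is still worded as rates, and the only comparisons named are unadjusted.

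**Conclusion.** The point holds in conditional form. The article does not fix whether scores or rates carry the main comparison, and its outcome wording leans to rates. If rates are compared, the loss at 20 against 20 is about 21 points of power by chi-square (79% to 58%) and 33 by Fisher (79% to 46%) for a 0.9 SD shift. For 0.6 SD it is about 15 points (46% to 30–31%) and 25 points (46% to 20–21%).

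These sizes rest on assumed effect sizes, normal scores, two-sided 5% and 50–80% of women above the cut-off before, because the article gives no such figures. The score had the higher power at every setting examined. Adjusting for ward and type of loss is a better method for non-randomised groups at little cost in precision. It reduces bias from these two sources only and leaves the effect of period confounded with calendar time.

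**What to change.** - **Primary outcomes and Quantitative analysis:** state that the main comparison for each scale (PGS total, EPDS total, DASS-21 scores) is a linear model of the score on period, adjusted for ward and type of loss. Collapse wards if some have few women. Report the adjusted mean difference with its 95% CI.
- **Cut-off rates:** keep them as secondary prevalence estimates with exact CIs, which serves the secondary objective.
- **Table 2:** list the comparison for the scale rows so that it agrees with the analysis section.
- **Wards contributing in one period only:** exclude them in a sensitivity analysis, not in the main one, so that a fixed 20 against 20 is not cut further.
- **Time since loss:** adjust for it only if the dates are recorded. It is not among the variables in Table 2.

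The cost is a change in the wording of the primary outcome and the analysis, with no new data for the two main covariates. About 4 degrees of freedom are spent, which is under one point of power if the covariates explain nothing and are balanced, and about four points at d = 0.9 under the imbalance assumed above. A mean difference is less intuitive than a rate, and reporting the rates alongside it meets that. The before/after time trend remains and should be stated as a limitation.

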#### Publishing the findings and results dissemination plan

Our findings will be published in peer-reviewed scientific journals (in English and Brazilian Portuguese). Moreover, the results will be locally shared with those involved in the design of the project, as a way to promote debates and reflections on the present praxis. It will also help create new measures for better outcomes in the future, which will affect the families who will experience stillbirth and neonatal death.

## Discussion

### Projection of the main findings

The approach to women and families who lost their babies during gestation, labor or post-partum period must follow a specific supportive guideline, which has to be locally adapted by Brazilian maternity wards. The way this issue has been addressed by health care professionals and the maternity wards may impact the process either positively or negatively. When negative emotions prevail, the technical approach might produce long-lasting, adverse psychological effects that might remain for a long time, sometimes even a lifetime.

The development of Brazilian supportive guidelines for perinatal loss, based on international experiences, may fill in an important gap regarding women’s health. It will be contemplated from a perspective focused on women’s sustainable development of wellbeing and empowerment. Additionally, our guidelines cover professional qualification. The staff that will be involved with this specific kind of care will interact to elaborate situational and contextualized scenarios to promote a better relationship between health care professional and patient.

The qualification of the bereavement professional is another relevant aspect of these guidelines. The Bereavement Professional will not only help professionals deal with specific and complex questions regarding grief, but also assist grieving families. He/she will address the private and individual matters of staff and professionals. These questions may be raised along with the assistance given to the families during the bereavement process. Among the Bereavement Professional’s tasks are the reorganization of staff, psychological support and empathic listening, whenever necessary.

### The contribution of this study to assist stillbirth and neonatal death

These supportive guidelines aim to assist women and families who are experiencing stillbirth and neonatal death. This assistance is grounded on empathy and efficiency during this challenging time. Moreover, it proposes continuity of care, including comforting the woman and her family, assisting the birth and designing care procedures after hospital discharge. This might contribute to the woman’s wellbeing and, consequently, her quality of life, as well as her mental and physical health. Likewise, the creation of standardized hospital procedures may provide the professionals more satisfaction at work, since occupational stress and communication anxiety are reduced, and unwanted obstetric outcomes are better managed. Notably, these guidelines will offer practical orientation towards technical routines related to the death of a baby during gestation. It will include corpse handling, memory box, among other routines.

### Obstetric applicability

The applicability of these guidelines will result in a pilot study. This way, the guidelines might be applied in similar scenarios. Moreover, based on our guidelines, other maternity wards or organizations will be able to design their own proposals for perinatal loss approach. They may use our findings to contemplate regional differences regarding perinatal bereavement, such as the ones in indigenous communities, *quilombolas*, favelas, and other groups.

### Anticipating main problems and proposing solutions

Dealing with death in childbirth facilities is a delicate situation. It might cause discomfort and privacy disruption in patients and professionals. We will try to minimize these problems and offer a clear outline of the objectives of the present investigation. We will highlight the benefits the project will bring to the family who is experiencing this trauma, and to the ones who will be in this situation in the future.

All participants will be granted the right to privacy throughout the research project. They may also stop participating any time they want. Authors/researchers who will deal directly with the participants are prepared to listen to them empathically and professionally and avoid any kind of embarrassment and discomfort this investigation may cause.

Finally, any problem or challenge professionals might have regarding bereavement will be addressed kindly, inside the health care establishment and, whenever necessary, will be handled by a qualified psychologist.

Some of the limitations and difficulties in this study can be accessed on Table 4.

**Table 4 Tab4:** Forecasting Difficulties: Mitigation Strategies

	Difficulties	Strategies to mitigate them
1	Participants may display strong emotions, such as sorrow, despair, anger, etc	Interviewers will be prepared for these situations and will interrupt and reschedule the interview if necessary
2	Participants may feel emotionally uncomfortable to share their experiences and feelings regarding the loss of the baby, since they are mourning	The questionnaire is very detailed and the fundamental information to understand the assistance is based on yes/no questions
3	Health care professionals may be experiencing grief in their lives. Also, bereavement situations may trigger previous feelings related to losses that happened in their professional or private lives. This might compromise or limit the assistance	The Bereavement Professional will pay close attention to this problem and may support the professional and/or reorganize the staff and substitute this member
4	The maternity ward might not have the resources to follow the new guidelines for perinatal bereavement	Limited resources are addressed by this project. It is possible to adjust them accordingly
5	Professionals and employees may feel some discomfort or find the guidelines morbid	The Reference Professional will help the professionals and the staff adjust to the new routine. More adapted professionals may join the staff to help transition
6	Difficulties regarding continuous care after hospital discharge	The professional from Regional Health Department XIII (Woman Health) will follow up on the implementation of the project and will address this problem
7	The maternity ward does not want to share data (women’s telephone numbers, emails, etc.)	The Project management staff understand that in the event the maternity ward does not want to share data, it may be included in the staff training, but not in data collection. Training and data collection are not imbricated

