### Pre-intervention

This phase will consist of two actions: (a) meetings with the focus group and (b) interviews with the women.*The pre-intervention focus group*During the pre-intervention focus group, an informed consent form will be signed, and participants will answer sociodemographic and work experience questionnaires. The meeting will last no longer than 1h30min.*The pre-intervention interview with women*

The pre-intervention interview with the women will be carried out by one of the researchers, based on the stillbirth and neonatal death list provided by the Reference Professional from the maternities ward. They will get in touch to schedule an in-person interview in a place to be defined. Information to verify inclusion and exclusion criteria will be covered. After inclusion criteria are met, the women will receive information concerning the study and will be invited to participate. If they accept, the in-person interview will be scheduled. During this meeting, the informed consent form will be signed. Afterwards, mental health scales will be applied. A qualitative interview will cover socioeconomic, demographic and behavioral data regarding the loss the woman went through.

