### Post-intervention

This phase consists of two actions: interviews with each woman in the post-intervention group and meetings with the post-intervention focus groups.

One focus group consists of the nurses in each maternity ward and the other is formed by the managers. The interviews and the meeting will mirror the steps taken in the pre-intervention phase.

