#### a) Participants and eligibility criteria

All four public maternity wards in Ribeirão Preto were invited to participate in this project and all of them accepted.

No exclusion criteria were outlined for health care professionals, employees and managers.

The *inclusion criteria* for women are:To live in one of the municipalities of the Ribeirão Preto region (XIII Regional Health Department, São Paulo State)Have experienced a stillbirth or a perinatal death during the estimated period^1^;Have faced the death of her baby in the following circumstances:Pregnancy that lasted more than 20 complete weeks;Had a baby weighing at least 500 g;Had a baby that died no later than twenty-eight days after the birth (neonatal death).

Women *exclusion criteria* are to not understand Portuguese and have severe mental health impairment.

The main difference between the pre- and post-intervention groups is the training process health care professionals will receive, together with preparing the maternity ward to implement local protocol. It is estimated that women who had a baby born in the pre-intervention group did not receive a care based on the supportive guidelines regarding perinatal bereavement.

The first 20 women from each group who accept to take part in this study will be interviewed.

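### The commitment to highlight the project's benefits, if carried out with women before the self-report scales, risks an expectation effect that differs between the before and after groups

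*Protocol article*

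**What the plan says.** The commitment is in the Discussion of the protocol article, under Anticipating main problems and proposing solutions. The section opens with the difficulty of dealing with death in childbirth facilities: "It might cause discomfort and privacy disruption in patients and professionals". As a remedy, the researchers will set out the study's objectives clearly, and "We will highlight the benefits the project will bring to the family who is experiencing this trauma". The sentence then continues: "and to the ones who will be in this situation in the future". It does not say when this is done.

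The order of contact with women is in Methods, Pre-intervention. After eligibility is checked, "the women will receive information concerning the study and will be invited to participate". At the interview itself, "During this meeting, the informed consent form will be signed. Afterwards, mental health scales will be applied". For the second period the Post-intervention section says: "The interviews and the meeting will mirror the steps taken in the pre-intervention phase".

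On exposure, the eligibility section states: "It is estimated that women who had a baby born in the pre-intervention group did not receive a care based on the supportive guidelines".

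The primary outcome is a composite of grief state and rates of depression, stress and anxiety. It rests on the PGS, EPDS and DASS-21, all described as self-applicable. Satisfaction with care is a questionnaire item in Table 2. Table 3 lists five possible biases, and response bias from what participants are told is not among them.

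**The concern.** The benefit to be highlighted is the study's own hypothesis. The Research question asks whether the guidelines lead to a healthier bereavement, Underlying hypotheses presupposes it, and Objectives makes the effect on mental health and grief the primary aim. The quoted sentence gives the benefit without qualification. A woman who hears it from the project's researchers and then rates her grief, mood and satisfaction may answer partly in line with it.

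An effect equal in both periods would largely cancel in the comparison. The difficulty is that the message means different things in the two periods. A post-intervention woman can take it as a description of the care she has just had. A pre-intervention woman is assumed not to have had that care, so for her it concerns other families. The comparison is unrandomised and between different women, so a difference of this kind cannot be separated from an effect of the guidelines. A Student t or chi-square test does not remove it; it has to be prevented at the interview.

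**Working it through.** **Step 1. Does the message reach women before the scales?**

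- The section on anticipating problems names patients and professionals together, so women are natural recipients but not the only ones. Timing is not stated.
- The Pre-intervention section fixes the order: study information, invitation, consent, then the scales. The Post-intervention section repeats these steps.
- Objectives and benefits are the usual content of study information. The article does not itself join the two sections, so exposure before the scales is likely but conditional.

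**Step 2. Would the effect differ by group?**

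| Part of the message | Pre-intervention woman | Post-intervention woman |
|---|---|---|
| Benefit to families bereaved now | Not true of her own care, as the protocol assumes | Can be true of her own care |
| Benefit to future families | Applies | Applies |

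The words may be identical. What differs is whether the first part can be true for the listener. The likely direction favours the intervention.

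**Step 3. How large could it be?**

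The plan gives no figure for such a shift. The sample size was set by convenience (20 + 20 = 40), with no alpha, power, effect size or SD, so there is no calculation to reproduce. What follows is illustration only. Assumptions: two-sided alpha 0.05, no true effect, and a difference between group means of d SD due to expectation alone.

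With n = 20 per group, df = 38 and noncentrality = d × √(n/2) = d × √10, the chance of p<0.05 is:

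| d (assumed) | Noncentrality | Chance of p<0.05 |
|---|---|---|
| 0 | 0 | 5% |
| 0.2 | 0.63 | 9% |
| 0.3 | 0.95 | 15% |
| 0.5 | 1.58 | 34% |
| 0.8 | 2.53 | 69% |

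For comparison, the difference detectable with 80% power is (1.960 + 0.842) × √(2/20) = 0.89 SD.

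The same shift can be put on the scale of a cut-off. Assume 60% of pre-intervention women are above it and the score is normal, so z = 0.253.

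- Shift of 0.2 SD: Φ(0.253 − 0.2) = Φ(0.053) = 52.1%, an apparent fall of about 8 points.
- Shift of 0.3 SD: Φ(0.253 − 0.3) = Φ(−0.047) = 48.1%, an apparent fall of about 12 points.

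In a group of 20 that is about 2 women (20 × 0.08 = 1.6; 20 × 0.12 = 2.4). The standard error of the difference is about √(0.6 × 0.4/20 + 0.5 × 0.5/20) = 0.157, or 16 points. A small shift would therefore seldom be significant by itself, but it would move the estimate. A moderate one would clearly raise the false-positive rate.

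**The case against.** The strongest reply is that the sentence may not be aimed at women. It stands in the Discussion, speaks of the family in the third person and deals with discomfort among professionals too. It would suit a talk to ward staff, some of whom Table 4 expects to find the guidelines morbid. The interview procedure mentions only study information. The invitation and consent wording is not available for this review, and the article is cautious about benefit elsewhere. This stands in part: recipient and timing are not fixed, so the point must remain conditional. But patients are named, and the protocol states the commitment without limiting it to staff or to a time after the scales.

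A reader might go further and infer that only post-intervention women will hear the message. The documents do not support that. The sentence also covers future families, the steps are mirrored, and no group-specific wording is given.

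It is also fair to say that EPDS and DASS-21 ask about symptoms in the past week and are less open to courtesy than satisfaction, which is not a primary outcome. In addition, post-intervention women will know from the memory box, leaflets and changed ward that their care was special, whatever the script says. Both remarks limit what a neutral script can achieve. Neither is a reason to add a statement of benefit. Finally, an unrandomised before/after study already has weak attribution. That is true, but this source of bias is avoidable at little cost.

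**Conclusion.** The concern holds in conditional form. The protocol commits the researchers to present as a benefit what the study is meant to test. If women hear this with the study information, it comes before every self-reported outcome. Because a benefit to the woman's own family can be true only in the post-intervention group, an expectation or courtesy effect may differ between periods and favour the guidelines. Table 3 does not recognise this.

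The size is unknown. The 60% baseline, the shifts of 0.2 to 0.8 SD and the alpha are assumptions, and the results in the working are conversions of them. A reader might infer that expectation by itself will produce the before/after difference. The documents show only that it could contribute. The point justifies a change of wording and order; it does not invalidate the design.

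**What to change.** 1. Replace the sentence under Anticipating main problems and proposing solutions, as far as it applies to women, with a commitment to one neutral information script used identically in both periods. The script discloses the purpose and procedures of the study and makes no claim of expected benefit before the scales.
2. Administer the PGS, EPDS, DASS-21 and the satisfaction items before any detailed discussion of the ward training or the memory-box programme. Fuller information can follow.
3. Add expectation and response bias to Table 3 as a residual limitation, since post-intervention women will already know what care they received.

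The change should not go as far as withholding all mention of the guidelines until the scales are complete. Pre-intervention places study information and consent before the scales, and Ethical and equity aspects says the consent form informs participants about the study. Only the unproven claim of benefit is dropped.

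The cost is a rewording of the invitation and information text, an ethics notification and a slightly less persuasive invitation.
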